### Data collection methods

Reasons for exclusion, withdrawal, discontinuation of the website program or the depression treatment plan, or loss-to-follow-up will be recorded. Table 1 provides an overview of the timeframe for all assessments and the measures that are used. All self-report measures, including sleep diary entries, will be collected via the study website at baseline, three and six-month time-points.

**Table 1 Tab1:** **Complete list of assessments and measures**

	**Recruitment/screening**	**Baseline assessment**	**Visit 1**	**Monitoring calls**	**Post-intervention follow-up assessment**	**Post-intervention follow-up assessment**	**6 Month post-intervention follow-up assessment**	**Early termination**
**Time-point (Week)**	**- 4**	**1**	**3**	**4 and 8**	**12**	**14**	**36**	
**Assessments**								
Informed consent	**X**	**X**						
Inclusion/exclusion criteria	**X**	**X**						
Self report measures		**X**		**X**	**X**		**X**	
Sleep diary		**X**			**X**		**X**	
Actigraphy		**X**			**X**			
Psychiatric assessment		**X**			**X**			**X**
Medical check-up*		**X**	**X**		**X**			
Monitor for suicidality*		**X**	**X**		**X**			**X**
Adverse events*			**X**		**X**			**X**
**Forms/measures**								
Depression (QIDS)	**X**							
Restless legs (RLS)	**X**							
Insomnia (ISI)	**X**	**X**		**X**	**X**		**X**	
Obstructive sleep apnea (Berlin questionnaire)	**X**							
Psychiatric diagnosis (SCID)		**X**			**X**			
Global functioning (GAF)		**X**			**X**			
Depression (HAM-D)		**X**	**X**		**X**			
Anxiety (HAM-A)		**X**			**X**			
Disease burden (CIRS-G)		**X**						
Social and occupational functioning (SOFAS)		**X**			**X**			
Cognition (MMSE)		**X**						
Depression (CES-D)		**X**		**X**	**X**		**X**	
Anxiety (STPI)		**X**			**X**		**X**	
Sleep (DBAS)		**X**			**X**		**X**	
Sleep (MEQ)		**X**						
Health and wellbeing (SF-12)		**X**			**X**		**X**	
Alcohol use (AUDIT)		**X**			**X**		**X**	
Physical activity		**X**			**X**		**X**	
Personality (Locus of control)		**X**						
Program evaluation					**X**			

*Additional clinical reviews will be scheduled on an individual basis in accordance with personalised depression treatment plan.

Key to Abbreviated Forms/Measures: QIDS (Quick Inventory of Depressive Symptomatology); RLS (Restless Legs Syndrome Rating Scale); ISI (Insomnia Severity Index); SCID (Structured Clinical Interview for DSM-IV Disorders); GAF (Global Assessment of Functioning); HAM-D (Hamilton Rating Scale for Depression); HAM-A (Hamilton Anxiety Rating Scale); CIRS-G (Cumulative Illness Rating Scale for Geriatrics); MMSE (Mini Mental State Examination); CES-D (Center for Epidemiologic Studies Depression Scale); STPI (State Trait Personality Inventory); DBAS (Dysfunctional Beliefs About Sleep Scale); MEQ (Morning-Eveningness Questionnaire); SF-12 (Short Form 12-Item Survey); AUDIT (Alcohol Use Disorders Identification Test).

All clinical (medical, psychiatric and actigraphy) data will be collected using standardised instruments and tools by staff trained in the trial protocol and procedures at baseline and three-months. All medical and psychiatry assessments will be performed at the Trial Coordinating Centre, whereas actigraphy data will be collected via the watch worn by participants in their homes. Clinicians will be given a hardcopy case record form (CRF) in which they will document results, including actigraphy, which will be downloaded when the watch is returned. Clinicians will be required to sign-off on the CRF on completion of each assessment.

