### Clinical treatment for depression

As part of standard treatment for depression, all participants will undergo a clinical assessment with a psychiatrist prior to study commencement, whereupon a depression treatment plan will be prepared in accordance with clinical practice guidelines [23,24]. This will include watchful waiting, referral to psychotherapy or other interventions such as couple therapy, or medication use under standard collaborative care with the patient’s GP. The assessment will include the Mood Episode and Disorder modules, and the Substance Abuse screens of the SCID, standard clinician rated measures: the 17-item Hamilton Rating Scale for Depression (HAM-D) [32], and the Hamilton Rating Scale for Anxiety (HAM-A) [33], Mini Mental State Examination [28], Global Assessment of Functioning (GAF) [34], Social and Occupational Functioning Assessment Scale (SOFAS) [35] and Cumulative Illness Rating Scale for Geriatrics (CIRS-G) [36] as well as completion of a full psychiatric and medical history. After two weeks, participants will be required to undergo a clinical review with the psychiatrist, in accordance with their treatment plan. Over the subsequent nine weeks, participants will undergo further psychiatric review and management as clinically required. Standard clinical instruments will be administered to monitor depressive symptoms over this period. If any changes to medication dosage are required, this will be discussed between the patient, trial psychiatrist and/or referring doctor. At the end of the trial period the participant will be referred back to their GP or treating doctor, or if required, managed in the trial clinic until appropriate for discharge.

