### Statistical methods

Primary outcome analysis will be undertaken on an intention-to-treat basis. Mixed-model repeated measures analyses will be used because of the ability of this approach to include participants with missing data. Characteristics of the participants including sociodemographics, physical activity, health and lifestyle factors will also be described by treatment group and overall. Safety criteria including adverse events and withdrawals will also be analysed. The type one error will be set at 5%. Descriptive statistics will include number of participants (N), mean, standard deviation, minimum, maximum and if a non- normal distribution, the median and first/third quartiles will be reported.

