### Harms

During the course of the study, participants will be assessed for both expected and unexpected adverse events (AEs) at each clinical and research assessment time point. Adverse events will be defined as any unfavourable and unintended sign, symptom or disease temporarily associated with the use of the intervention under investigation. Medical conditions or diseases present before starting the intervention will be considered adverse events only if they worsen after starting the trial and that worsening is considered to be related to the study intervention. An AE will also be extended to include any undesirable and unintended effect of research occurring in trial participants as a result of the collection of identifiable private information under the research. An AE will be deemed serious if it is determined to be associated, or possibly associated with study involvement, and results in either: death, is life-threatening, requires or prolongs hospitalisation, or results in persistent or significant disability or incapacity. Expected AEs will include: initial discomfort or embarrassment due to personal or sensitive nature of research questions; concerns related to internet-based data collection and storage procedures; and initial tiredness, fatigue and possible concentration problems as a result of sleep restriction techniques to improve sleep habits.

Adverse events will be detected at the Week 3 clinical review and Week 12 follow-up assessment. In addition, research assistants conducting routine monitoring telephone interviews at Weeks 4 and 8, will also have capacity to detect AEs.

All AEs (including Serious Adverse Events, or SAEs), regardless of relatedness to the interventions under investigation, will be recorded, classified and graded on an adverse event form. Recording will be completed in a concise manner using standard, acceptable medical terms. All SAEs will be reported to the Human Research Ethics Committee within 72 hours.

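### Adverse events are looked for at every clinical review, and part of the review schedule after randomisation follows mood, so the arms may be looked at unequally often and the all-event comparison may be distorted

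*Protocol article*

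**What the plan says.** All places are in the protocol article.

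- **When adverse events are sought.** Harms gives a general rule: "participants will be assessed for both expected and unexpected adverse events (AEs) at each clinical and research assessment time point". It then names fixed points: "Adverse events will be detected at the Week 3 clinical review and Week 12 follow-up assessment". Of the calls it says that "research assistants conducting routine monitoring telephone interviews at Weeks 4 and 8, will also have capacity to detect AEs".
- **Table 1.** The row "Adverse events" is marked at Week 3, Week 12 and early termination, but not in the column for the Week 4 and 8 calls. The suicidality row is not marked at the calls either. Both rows, and the medical check-up row, carry an asterisk whose footnote reads: "Additional clinical reviews will be scheduled on an individual basis in accordance with personalised depression treatment plan".
- **What drives additional reviews.** Clinical treatment for depression states: "Over the subsequent nine weeks, participants will undergo further psychiatric review and management as clinically required". Participant monitoring and program adherence adds that a man whose mood has worsened is referred to his psychiatrist, and that safety monitoring takes place at each review.
- **What SHUTi should change.** The Background hypothesises a greater improvement in depression on SHUTi than on control.
- **Analysis.** Statistical methods says: "Safety criteria including adverse events and withdrawals will also be analysed". It does not separate contacts scheduled for everyone from additional reviews.

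**The concern.** Part of the opportunity to record an adverse event depends on how a man's depression goes after allocation, and that course is the outcome the trial hopes to shift. If mood improves more on SHUTi, control men may be reviewed more often and have more events written down, which makes SHUTi look safer than it is. If mood worsens on SHUTi, or tiredness from restricted time in bed brings men back to the clinic, the distortion runs the other way. Blinding the psychiatrist does not prevent this, because reviews follow mood and not known allocation.

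The stake is the safety comparison. Safety and event monitoring names one concern for SHUTi, tiredness and its consequences, and mild tiredness may be recorded only if someone asks. The same section plans no independent safety committee. If the form does not record the kind of contact at which an event was found, a later analysis may be unable to separate the two kinds.

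**Working it through.** **Step 1: the plan's own figure.** The only related number is the sample size: 36 per group after 10% attrition, and 36 / 0.9 = 40 per group, as stated. No event rate or number of reviews is given, so everything below is illustration.

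**Step 2: recorded-event ratio with no true difference.** Let F be the looks common to all men, E_S and E_C the mean additional reviews on SHUTi and control, and r the share of events seen at an additional review that a later common contact would have picked up anyway. With the same event rate per look in both arms, the rate cancels:

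ratio = [F + (1 − r)E_S] / [F + (1 − r)E_C]

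F = 4 counts Weeks 3, 4, 8 and 12. F = 2 counts only Weeks 3 and 12, the fixed points marked in Table 1. The values of E and r are assumptions.

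| F | E_S v E_C | r = 0 | r = 0.5 | r = 1 |
|---|---|---|---|---|
| 4 | 1 v 1 | 5/5 = 1.00 | 1.00 | 1.00 |
| 4 | 1 v 2 | 5/6 = 0.83 | 4.5/5 = 0.90 | 1.00 |
| 4 | 1 v 3 | 5/7 = 0.71 | 4.5/5.5 = 0.82 | 1.00 |
| 2 | 1 v 2 | 3/4 = 0.75 | 2.5/3 = 0.83 | 1.00 |
| 4 | 2 v 1 | 6/5 = 1.20 | 5/4.5 = 1.11 | 1.00 |

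The last row is the opposite direction.

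**Step 3: men with at least one recorded event.** With the same per-look probability p in both arms, Poisson additional reviews and no recall, the probability is 1 − (1 − p)^F × exp(−pE). For 1 v 2 additional reviews (SHUTi v control):

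| F | p = 0.05 | p = 0.10 | p = 0.20 |
|---|---|---|---|
| 4 | 22.5% v 26.3% | 40.6% v 46.3% | 66.5% v 72.5% |
| 2 | 14.2% v 18.3% | 26.7% v 33.7% | 47.6% v 57.1% |

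The spurious gap is 4 to 6 points with four common looks and 4 to 10 points with two. It is zero for 1 v 1.

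**Step 4: masking.** A true 20% excess on SHUTi with 5 v 6 looks and no recall is recorded as 1.2 × 5/6 = 1.00.

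**Step 5: a test, if one were made.** With 40 men per arm and 0.3 events per look, 5 v 6 looks gives 40 × 5 × 0.3 = 60 v 40 × 6 × 0.3 = 72 expected events, and 5 v 7 gives 60 v 84. A 5% Poisson comparison with no true difference then rejects in about 18% and 52% of simulated trials. At 0.1 events per look these fall to 10% and 21%, and at 0.05 to 7% and 13%.

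**Step 6: common contacts only.** The terms in E drop out, both arms have the same planned looks, and the ratio is F/F = 1.00.

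**Step 7: which contacts are common.** Under Trial design the program starts after the two-week baseline, so the Week 3 review carries little or no program exposure. That leaves Week 12, plus Weeks 4 and 8 if the calls elicit adverse events. On this Harms and Table 1 do not agree.

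**The case against.** Four arguments deserve weight.

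- **Analysis detail belongs in the analysis plan.** Which adverse events are tabulated, and with what denominator, is commonly left there, and its absence from an article is no fault. This stands for the analysis. It does not stand for collection: need-driven looks are fixed in this document, and an unrecorded contact type may not be recoverable later.
- **Some additional reviews are set before allocation.** The footnote ties them to the treatment plan, which is prepared before study commencement, and Allocation places randomisation after the psychiatrist's decision to enrol. Reviews fixed by that plan are balanced by randomisation. This stands, and it confines the concern to reviews prompted by need or worsening mood.
- **Recall shrinks the effect.** If a later contact asks about the whole interval, additional looks add few events. This stands. The r = 1 column shows no distortion.
- **Suicidality found because a man worsened is partly a real difference.** This also stands, and it is a reason to keep the all-event table.

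A reader might infer that the arms' event rates certainly rest on unequal looks. The article does not support that. Looks will differ between men, but the arms differ on average only if mood courses differ enough to change scheduling, and Sample size expects only a small to moderate added effect. A reader might also take 18% or 52% as the trial's false-positive rate. Those figures need an assumed event rate, assumed review counts, no recall and a between-arm test that Statistical methods does not name.

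**Conclusion.** The point holds as a risk of distortion. Adverse events and suicidality are assessed at clinical reviews, part of the review schedule after randomisation follows need and worsening mood, and SHUTi is hypothesised to change mood. An all-event comparison could therefore understate or overstate a SHUTi harm, despite blinding.

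The size cannot be derived from the article. Under the assumptions shown, the ratio with no true difference lies anywhere from 0.71 to 1.20, and it is 1.00 if the arms have equal reviews or if recall is complete. Masking of a modest true excess matters more here than a false alarm. It would also be wrong to conclude that events found at additional reviews should be left out: they are safety data, and removing them from the report could itself hide a harm.

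**What to change.** 1. Add a contact-type field to the adverse event form: scheduled for all, additional review, or early termination.
2. Reconcile Harms with Table 1 on whether the existing Week 4 and 8 calls elicit adverse events. If they do, ask every participant the same adverse-event question at those calls and mark it in the table.
3. Keep the table of all events by arm. Beside it, compare the arms on contacts scheduled for everyone after the program starts: adverse events at Weeks 4, 8 and 12 if the calls elicit them, otherwise at Week 12; suicidality at Week 12. Show Week 3 separately as before program start. Count an event already noted at an additional review if the man reports it again at the next scheduled contact; otherwise the restriction removes events from the arm reviewed more often.
4. Report the number of additional reviews per participant by arm.

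The cost is one form field, one more table and a few lines of wording. The scheduled-contact comparison uses fewer events and is less precise. Clinical scheduling is unchanged and no safety data are lost.

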### Data management

All consenting participants will be allocated a unique identifier at the time of preliminary screening and this identifier will be used exclusively to link all data collected as part of the trial. All self-report data will be collected via the secure internet site that delivers both arms of the treatment program (intervention and control). This data will be held on a secure server maintained by the provider of the internet-delivered interventions, BeHealth Solutions, and will only be transferred to the secure master trial database at the Trial Coordinating Centre at trial-end.

All clinical data (medical, psychiatric and actigraphy) will be entered electronically into the master trial database by suitably qualified staff, supervised by the trial manager. Data will be entered into a user-friendly Filemaker platform and integrity will be enforced through a variety of mechanisms, including referential data rules, valid values, range checks and consistency checks. The option to choose a value from a list of valid codes will also be available when applicable. The master trial database will be held on a secure server hosted by the Faculty of Medicine, University of Sydney. The trial database will be password protected, and only authorised trial personnel will have access. The database will be maintained in accordance with University of Sydney Information and Communication Technology policy and procedures. Upon database lock, data will be exported to a statistical software package for subsequent analysis.

### Statistical methods

Primary outcome analysis will be undertaken on an intention-to-treat basis. Mixed-model repeated measures analyses will be used because of the ability of this approach to include participants with missing data. Characteristics of the participants including sociodemographics, physical activity, health and lifestyle factors will also be described by treatment group and overall. Safety criteria including adverse events and withdrawals will also be analysed. The type one error will be set at 5%. Descriptive statistics will include number of participants (N), mean, standard deviation, minimum, maximum and if a non- normal distribution, the median and first/third quartiles will be reported.

### Data monitoring

The accuracy, completeness and progress of data will be monitored continuously throughout the trial. Each CRF will have a data checklist attached, on which the assessments completed and other information will be recorded. Any missing information or illegible data will be queried with the researcher, clinician or interviewer responsible for its collection. Audits will be undertaken periodically to ensure that all data relating to informed consent, self-report questionnaires, medical and psychiatric assessment, and actigraphy, are accounted for, and that psychiatric assessments are standardised. All original CRFs will be stored securely by trial identification number at the Trial Coordinating Centre.

Following data entry into the master trial database, data will be randomly checked for accuracy and completeness and verified against source data. Approximately 5% of participants will be specifically monitored.

### Safety and event monitoring

The intervention under study is considered low-risk, with the only safety concern associated with the active SHUTi intervention related to increased tiredness and its sequelae due to restricted time spent in bed (as per the behavioural treatment for insomnia). This risk is mitigated directly through the program, which does not restrict sleep by fewer than five hours. In light of this, and given that all trial participants will be under the clinical care of their treating psychiatrist throughout the intervention period, an independent Data and Safety Monitoring Committee will not be established.

### Harms

During the course of the study, participants will be assessed for both expected and unexpected adverse events (AEs) at each clinical and research assessment time point. Adverse events will be defined as any unfavourable and unintended sign, symptom or disease temporarily associated with the use of the intervention under investigation. Medical conditions or diseases present before starting the intervention will be considered adverse events only if they worsen after starting the trial and that worsening is considered to be related to the study intervention. An AE will also be extended to include any undesirable and unintended effect of research occurring in trial participants as a result of the collection of identifiable private information under the research. An AE will be deemed serious if it is determined to be associated, or possibly associated with study involvement, and results in either: death, is life-threatening, requires or prolongs hospitalisation, or results in persistent or significant disability or incapacity. Expected AEs will include: initial discomfort or embarrassment due to personal or sensitive nature of research questions; concerns related to internet-based data collection and storage procedures; and initial tiredness, fatigue and possible concentration problems as a result of sleep restriction techniques to improve sleep habits.

Adverse events will be detected at the Week 3 clinical review and Week 12 follow-up assessment. In addition, research assistants conducting routine monitoring telephone interviews at Weeks 4 and 8, will also have capacity to detect AEs.

All AEs (including Serious Adverse Events, or SAEs), regardless of relatedness to the interventions under investigation, will be recorded, classified and graded on an adverse event form. Recording will be completed in a concise manner using standard, acceptable medical terms. All SAEs will be reported to the Human Research Ethics Committee within 72 hours.

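### The Harms section makes seriousness, and the counting of a worsening pre-existing condition, depend on judged relatedness, so SAEs and worsening can be under-counted; Table 1 also disagrees with the text on when AEs are collected

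*Protocol article*

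**What the plan says.** All the definitions are in the Harms section of the protocol article.

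- **Seriousness:** "An AE will be deemed serious if it is determined to be associated, or possibly associated with study involvement, and results in either: death", followed by the other usual grave outcomes.
- **Pre-existing conditions:** these are adverse events "only if they worsen after starting the trial and that worsening is considered to be related to the study intervention".
- **Recording:** "All AEs (including Serious Adverse Events, or SAEs), regardless of relatedness to the interventions under investigation, will be recorded, classified and graded".
- **Expedited reporting:** "All SAEs will be reported to the Human Research Ethics Committee within 72 hours".
- **Timing in the text:** participants will be "assessed for both expected and unexpected adverse events (AEs) at each clinical and research assessment time point". The section then says "Adverse events will be detected at the Week 3 clinical review and Week 12 follow-up assessment", and adds that the research assistants who telephone at Weeks 4 and 8 are also able to pick up AEs.
- **Timing in Table 1:** the row "Adverse events" is marked at Visit 1 (Week 3), the Week 12 assessment and early termination. Its asterisk refers to further clinical reviews arranged individually. The columns for the Week 4 and 8 calls and for Week 36 are blank.

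Three other sections bear on the point. Eligibility criteria requires every participant to have a current depressive disorder and insomnia symptoms above threshold. Safety and event monitoring says that no independent data and safety monitoring committee will be set up. Statistical methods says that adverse events and withdrawals will be analysed, and applies no relatedness filter.

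**The concern.** Whether an event happened, how grave it was and what caused it are three separate questions. Here the answer to the third decides the other two. An event with a fatal or hospitalising outcome loses the serious label if someone judges it unconnected with the study. A worsening of depression or insomnia is not an adverse event at all if someone judges it unrelated to the program.

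In this trial the second rule covers the most relevant harms, because the pre-existing conditions are the ones under treatment. The first rule decides what the ethics committee hears within 72 hours. With no independent safety committee, that report is the only outside safety check the article names. The trial is also meant to inform a definitive trial, and an SAE count kept low by definition would mislead that decision.

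The schedule raises a smaller issue. The text and Table 1 do not agree on whether AEs are collected at the telephone calls, which are the only study-wide fixed contacts during the exposure period after its opening week.

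**Working it through.** The plan states no event rate or safety figure, so there is no number to reproduce. The check applies the definitions to each kind of event and then sets the contact weeks against the exposure window.

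**Step 1. Apply the definitions as written.** I assume the general AE definition rests on association in time with use of the intervention, so that a new-onset event needs no causal judgement to count.

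| Event after the start | Judged | Counted as AE? | Counted as SAE? | 72-hour report? |
|---|---|---|---|---|
| New-onset, non-serious | unrelated | yes | not applicable | not applicable |
| New-onset, death or hospitalisation | unrelated | yes | no | no |
| Worsening of pre-existing condition, non-serious | unrelated | no | not applicable | not applicable |
| Worsening of pre-existing condition, with hospitalisation | unrelated | no | no | no |
| New-onset or worsening, grave outcome | related | yes | yes | yes |

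Row 1 is unaffected by the wording. Row 2 keeps its AE record but loses the serious label and the report. Rows 3 and 4 drop out of the AE record altogether.

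**Step 2. Compare the two causal tests.** Seriousness asks about association, or possible association, with study involvement. Worsening asks whether it is considered related to the intervention, which is a narrower question and makes no allowance for a merely possible link. A worsening that is possibly connected with study involvement, but not considered related to the intervention, is not an AE. It therefore never reaches the more generous seriousness test.

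**Step 3. Compare with the recording rule.** The promise to record events regardless of relatedness can be kept for row 1. It is kept only in part for row 2, where the event is recorded but not as serious. It cannot be kept for rows 3 and 4, because relatedness has already decided whether there is an AE to record.

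**Step 4. Lay contacts against exposure.** A two-week baseline followed by nine weeks of program access puts exposure at about Weeks 3 to 11.

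| Contact | Week | Inside Weeks 3–11? | AE row marked in Table 1? |
|---|---|---|---|
| Visit 1 | 3 | yes, at the start | yes |
| Monitoring call | 4 | yes | no |
| Monitoring call | 8 | yes | no |
| Post-intervention | 12 | no, just after | yes |
| Six-month follow-up | 36 | no | no |

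Between the fixed weeks marked in Table 1 the gap is 12 − 3 = 9 weeks. If the calls count as AE contacts, the gaps are 4 − 3 = 1, 8 − 4 = 4 and 12 − 8 = 4 weeks. Which of these describes the trial depends on whether the text or the table is followed.

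**The case against.** Much of the case on the other side stands, and it limits the point.

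- **Timing.** A reader of Table 1 alone might infer that nobody checks for harm between the start and the end of exposure. The documents do not support that. The text gives the Week 4 and 8 callers the ability to pick up AEs. They also collect mood and insomnia measures, and men whose mood deteriorates are referred to the psychiatrist. Safety monitoring takes place at every clinical review, and further reviews are arranged individually. What remains is a mismatch between text and table, and wording that permits detection at the calls without committing anyone to ask.
- **Scope.** A reader might also infer that harms as a whole are systematically under-counted. That is too broad. New-onset events are recorded and graded whatever their cause, and the planned safety analysis is not restricted to related events.
- **Worsening mood is not lost as data.** The CES-D is collected at baseline, Weeks 4, 8, 12 and 36. The HAM-D is collected at baseline, Week 3 and Week 12, and suicidality has its own row in Table 1. None of these depends on a causal judgement. They do not replace an AE or SAE record, however: a mean score does not show an admission, and it does not reach the ethics committee.
- **Different referents.** Study involvement and the interventions are not the same thing, so an SAE could be linked to the first and not the second. This softens the conflict with the recording rule for seriousness. It does not help with worsening conditions, where the definition and the recording rule both turn on the intervention.
- **Blinded judgement.** Staff who do not know the arm are less likely to classify events differently by arm. That protects the comparison between arms, but not the absolute count or the expedited report.
- **Size.** One could note that zero events in 40 men gives a one-sided 95% upper bound of 1 − 0.05^(1/40) = 7.2%, or that two unlabelled admissions would be 2/40 = 5% of an arm. These are illustrations and do not measure misclassification.

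**Conclusion.** The definitional fault holds. As written, deaths, life-threatening events and hospitalisations judged unrelated are not SAEs and fall outside the 72-hour report. Worsening depression or insomnia judged unrelated is not an AE. These rules conflict with the section's own recording promise: fully for worsening conditions, in part for seriousness. The counts that can fall short are SAEs and worsening of pre-existing conditions; new-onset non-serious AEs are not affected.

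The size cannot be computed, since the documents give neither event rates nor the share likely to be judged unrelated. For scale only, each event that goes uncounted moves an arm of 40 by 1/40 = 2.5 percentage points.

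The schedule point is separate and smaller. The text and Table 1 disagree about AE collection at the Week 4 and 8 calls, and the general sentence on timing also covers Week 36, which the table leaves blank. The primary efficacy analysis is not touched.

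The conclusion rests on staff applying the printed definitions literally, and on reading the general AE definition as one of timing.

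**What to change.** In the Harms section:

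1. Define an SAE by outcome alone, using the outcomes already listed.
2. Count any worsening of a pre-existing condition after the start as an AE.
3. Record relatedness as a separate field that affects neither the counting of AEs and SAEs nor the 72-hour report.

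In Table 1 and the timing text:

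4. Add a structured AE question to the existing Week 4 and 8 calls and mark it in the AE row.
5. State whether AEs are asked about at Week 36, so that the general sentence on timing and the table agree.

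The change takes a few sentences and one table row. The downside is a few extra forms and ethics reports, and a few minutes on calls that are already made. Design, sample size and treatment stay as they are.
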